## Abstract

**Introduction:**

High morbidity and mortality rates of proven bacterial infection are the main reason for substantial use of intravenous antibiotics in neonates during the first week of life. In older children, intravenous-to-oral switch after 48 hours of intravenous therapy has been shown to have many advantages and is nowadays commonly practised. We, therefore, aim to evaluate the effectiveness, safety and cost-effectiveness of an early intravenous-to-oral switch in neonates with a probable bacterial infection.

**Methods and analysis:**

We present a protocol for a multicentre randomised controlled trial assessing the non-inferiority of an early intravenous-to-oral antibiotic switch compared with a full course of intravenous antibiotics in neonates (0–28 days of age) with a probable bacterial infection. Five hundred and fifty patients will be recruited in 17 hospitals in the Netherlands. After 48 hours of intravenous treatment, they will be assigned to either continue with intravenous therapy for another 5 days (control) or switch to amoxicillin/clavulanic acid suspension (intervention). Both groups will be treated for a total of 7 days. The primary outcome will be bacterial (re)infection within 28 days after treatment completion. Secondary outcomes are the pharmacokinetic profile of oral amoxicillin/clavulanic acid, the impact on quality of life, cost-effectiveness, impact on microbiome development and additional yield of molecular techniques in diagnosis of probable bacterial infection.

**Ethics and dissemination:**

This study has been approved by the Medical Ethics Committee of the Erasmus Medical Centre. Results will be presented in peer-reviewed journals and at international conferences.

**Trial registration number:**

NCT03247920

Strengths and limitations of this studyThis study addresses an important clinical question regarding intravenous-to-oral antibiotic switch in neonatal care.The results of this study can be included in antibiotic stewardship programmes.A non-inferiority study design is used.The primary outcome assessment is challenging since it is impossible to state whether a new infection episode is a true reinfection since cultures of the first infection were sterile.Only probable bacterial infections are included in this study, thus, results cannot directly be applied to culture-proven infection.

## Introduction

Antibiotics are among the most prescribed drugs in the paediatric population. With increasing concerns regarding microbial resistance leading to potential multidrug resistant infections, antibiotic stewardship programmes have been developed. The main goal of these programmes is optimisation of the use of antibiotics. Moreover, unnecessary use should be reduced since antibiotics do interfere with the development of the gut microbiome in early stages of life, influencing the risk of developing several diseases such as asthma, diabetes and obesity later in life.^1–3^ Initially started in adult population, these programmes have, since then, been implemented in the paediatric field, starting with the formation of the Pediatric Committee on Antimicrobial Stewardship (AS) by the Paediatric Infectious Diseases Society in 2010. One of the principles of AS is the appropriate and timely de-escalation of antibiotic use including a switch from parenteral to oral therapy in clinically well children. An early intravenous-to-oral switch leads to many advantages such as a reduction in hospital stay and associated health costs and is currently described in several guidelines.^4^

However, oral switch therapy is not yet widely practised in neonates. When a bacterial infection is suspected, either based on maternal risk factors or subtle clinical symptoms, antibiotic therapy is immediately started. In the best-case scenario, symptoms disappear, inflammatory parameters are reassuring and cultures remain negative after which therapy can be stopped after 36–48 hours. In some of the neonates (~1% of living births), the presence or absence of a bacterial infection cannot be established.^5^ They may have elevated inflammatory parameters and show clinical signs, although (blood) cultures remain sterile; so-called ‘probable bacterial infection’. In such cases, antibiotic therapy is usually continued intravenously, up to 7 days.^6^

In low-income and middle-income countries, the above practice is not common due to limited resources. The need for good home-based antibiotic treatment to reduce mortality following neonatal infections has led to several large randomised trials on the use of oral antibiotics. These studies showed that a simplified regimen with a switch to oral amoxicillin after 48 hours is as effective and safe as parenteral therapy.^7–9^ Results of those studies have been incorporated in WHO guidelines for the management of neonatal sepsis.^10^ Unfortunately, the outcomes cannot be applied to a higher income setting since the studies were based on clinical symptoms solely and no diagnostic tests were performed. This approach has not yet led to further research in high-income settings.

Several small studies have been published on the use of different oral antibiotics, evaluating both pharmacokinetics (PKs) and clinical efficacy. Regarding PKs, studies have commonly found that adequate antibiotic serum levels can be reached following oral administration, although peak levels are lower and appear later in time compared with parenteral administration. Furthermore, a great interindividual variation was seen.^11 12^ Small efficacy studies evaluating an early-oral switch in neonates with a possible or proven infection are promising. In a cohort study, 222 infants with possible and proven group B streptococcal (GBS) infection switched to oral amoxicillin in a high dosage after 48 hours of intravenous treatment. During the 3-month follow-up period, no reinfections occurred.^13^ Similar results were found in a case–control study in which 36 infants with a possible or proven bacterial infection switched to oral cefpodoxime on day 3. No increase in reinfection rate was observed and the benefits of oral therapy included reduction of hospital stay and an increase in the number of exclusively breastfed newborns.^13 14^ Unfortunately, study sizes were small and studies were not randomised. Furthermore, no full cost-effectiveness analyses of paediatric intravenous-to-oral switch therapy have been reported to date. This represents an important knowledge gap, considering that, in the current era of austerity and rising healthcare costs, it is increasingly required to demonstrate whether or not new treatment strategies offer good value for money.

Together with uncertainties about bioavailability after oral administration, the lack of firm evidence delays further implementation in a high-resource setting. When intravenous-to-oral antibiotic switch therapy in neonatal infections is proven safe and effective, it can lead to a great improvement in quality of life (QOL) for both child and parents. Furthermore, it can reduce the length-of-hospital stay, which will have positive effects on rising healthcare costs.

### Objectives

The primary objective is to demonstrate non-inferiority of intravenous-to-oral antibiotic switch therapy in clinically well neonates with a probable bacterial infection compared with a complete course of intravenous therapy. The secondary objectives are: (1) to describe PKs of oral amoxicillin/clavulanic acid in neonates; (2) to quantify the cost-effectiveness of intravenous-to-oral switch therapy in neonates; (3) to evaluate the QOL in relation to switch therapy in neonates; (4) to study modification of the gut microbiome in relation to type and administration of antibiotics and (5) to explore the additional value of molecular diagnostics on bacterial infection using left-over blood culture material that remains after culture time has passed.

## Methods and analysis

### Study design

The RAIN study (Reduction of intravenous Antibiotics In Neonates) is a multicentre, randomised controlled, open label, non-inferiority trial. Patients will be recruited in 17 large teaching hospitals in the Netherlands. For details on participating hospitals, we refer to the online supplementary material.

10.1136/bmjopen-2018-026688.supp1Supplementary data

### Participants

Neonates are eligible for participation if they have a postmenstrual age of 35 weeks or more, are 0–28 days old, have a body weight of at least 2 kg and have a ‘probable bacterial infection’ based on clinical symptoms or maternal risk factors and elevated inflammatory parameters for which the paediatrician has decided to complete a full course of intravenous antibiotics. A C reactive protein (CRP) level of ≥10 mg/L is considered as elevated. For procalcitonin (PCT), we refer to the age-adapted ranges.^15 16^ Clinical symptoms can be found in the online supplementary material. All neonates with a proven bacterial infection, for example, positive blood or cerebrospinal fluid culture or a severe clinical sepsis requiring intensive care treatment are excluded from participation. Inclusion and exclusion criteria are described in table 1. Participants will be screened by the local paediatrician or investigator and randomised after 48 hours of intravenous treatment once informed consent has been obtained.

**Table 1 T1:** Inclusion and exclusion criteria Reduction of intravenous Antibiotics In Neonates study

Inclusion criteria	Exclusion criteria
Neonates, postmenstrual age ≥35+0 weeks, postnatal age of 0–28 days, body weight ≥2 kg. Probable bacterial infection defined as clinical symptoms and/or maternal risk factors and elevated inflammatory markers for which empiric broad-spectrum antibiotic treatment was initiated and needs to be continued for >48 hours. Clinically well. Tolerate oral feeding without overt vomiting.	Proven bloodstream infection. Absence of blood culture. Severe localised infection (meningitis, osteomyelitis, necrotising enterocolitis). Severe clinical sepsis (compromised circulation, need for mechanical ventilation). Continuous need for a central venous line. Severe hyperbilirubinaemia exceeding the exchange level. Parents’ inability to administer medication.

### Intervention

The intervention group will switch to oral amoxicillin/clavulanic acid after 48 to 72 hours of intravenous antibiotics. The number of intravenous antibiotic doses prior to the switch will be recorded for every participant. The control group will receive the full course of intravenous antibiotics, which consists of penicillin and gentamicin, in case of early-onset sepsis, in most participating centres. Both groups will be treated for a total of 7 days. The trial flow diagram is outlined in figure 1.

**Figure 1 F1:**
[figure not shown]
Flow chart of study procedures. ^1^CRP, C reactive protein; PCT, procalcitonin; RAIN, Reduction of intravenous Antibiotics In Neonates.

#### Dosage, method of administration

A daily oral dose of 75/18.75 mg/kg of amoxicillin/clavulanic acid, thus 25/6.25 mg/kg every 8 hours, will be administered. The mode of administration is orally via suspension, or in case of feeding problems (with the exception of vomiting) per nasopharyngeal tube. If the neonate vomits significantly within 30 min after administration, the administration will be repeated.

### Randomisation and blinding

Participants will be randomised after 48 hours of intravenous treatment by a web-based programme according to a stratified block randomisation (stratified per site in alternated blocks of 2 and 4). Randomisation ratio will be 1:1. Randomisation can under no circumstances be influenced by the study team. If parents want their child to be in a specific group, they will be excluded from participation. Patients and healthcare professionals will not be blinded, because of the nature of treatments (intravenous vs oral therapy); the primary investigators performing the statistical analysis will be blinded for the allocated treatment.

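### Site-stratified blocks of 2 and 4 in an open-label trial leave upcoming allocations partly predictable to the staff who screen: about 11% to 39% certain, depending on how 'alternated' is read

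*Protocol article*

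**What the plan says.** The section Randomisation and blinding of the protocol article fixes four things:

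- **Mechanism:** "Participants will be randomised after 48 hours of intravenous treatment by a web-based programme".
- **Scheme:** block randomisation, "stratified per site in alternated blocks of 2 and 4".
- **Ratio:** "Randomisation ratio will be 1:1".
- **Blinding:** "Patients and healthcare professionals will not be blinded, because of the nature of treatments".

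The same section gives an assurance: "Randomisation can under no circumstances be influenced by the study team". It also excludes infants whose parents want a particular arm.

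The section Participants says who decides on entry: "Participants will be screened by the local paediatrician or investigator and randomised after 48 hours of intravenous treatment once informed consent has been obtained". Several criteria need local judgement, among them whether the infant is clinically well, whether the infection counts as probable and will be treated for the full course, and whether the parents are able to give the medication.

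The article does not say whether the order of block sizes is random, or whether the sizes are kept from the sites.

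**The concern.** Allocation concealment requires that whoever decides to enter a patient cannot foresee the arm. Three stated features work against this together: small blocks, stratification by site, and open treatment. Anyone at a site can keep a running count of oral and intravenous allocations. Each block is balanced, so the arm that lags at the site is also the arm that lags in the current block, and it is the likelier next assignment. If the sizes and their order are known, some assignments are certain.

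The people in this position also judge eligibility and choose whom to approach, and when. They could act on a prediction before randomisation without touching the allocation system. Neither the intention-to-treat nor the per-protocol analysis repairs selection at that stage. With very few primary events expected, a shift in the risk mix of a few infants could matter to the non-inferiority conclusion.

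**Working it through.** **Inputs.** Block sizes 2 and 4, by site, 1:1, open label (Randomisation and blinding); 17 hospitals (Study design); 550 infants, 275 per arm, a 1% event rate in both arms and a 3% margin (Power calculation). The mean site size is 550/17 = 32.4, so 32 is used below.

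**The plan's own figures.** The article gives no predictability figure to reproduce. Its sample size reproduces to rounding: 2 × 0.01 × 0.99 × (1.960 + 1.282)² / 0.03² = 231.2, against 231 stated. The block scheme does not affect it.

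**Certain allocations.** An allocation is certain once one arm has used its quota in the current block.

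- Block of 2: the second is always certain, which gives 1 certain allocation.
- Block of 4: the fourth is always certain. The third is certain when the first two match, with probability 1/3. This gives 1 + 1/3 = 4/3.

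*Strict alternation, start known.* Per cycle of six, (1 + 4/3)/6 = 7/18 = 38.9%, or 550 × 7/18 ≈ 214 allocations. A site of 32 that starts with a block of 2 has five full cycles plus one block of 2: (5 × 7/3 + 1)/32 = 39.6%.

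*Strict alternation, start unknown.* Simulating an observer who updates on each allocation at a site of 32 gives about 31%.

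*Random order, each size equally likely.* Certainty arises only when the site count differs by 2, which reveals a block of 4 whose first two allocations matched. The last two are then certain. Per block: 1/2 × 1/3 × 2 = 1/3. The mean block length is 3, so the share is (1/3)/3 = 1/9 = 11.1%; simulation at 32 per site gives 10.7%.

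**Best guess.** Guess the lagging arm, or toss a coin when the arms are level. Enumeration gives 3/2 correct in a block of 2 and 17/6 in a block of 4, so (3/2 + 17/6)/6 = 4.333/6 = 72.2%.

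**Comparison at 32 infants per site, for an observer who knows the sizes:**

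| Scheme | Certain | Best guess |
|---|---|---|
| 2 and 4, strict, start known | 39.6% | 72% |
| 2 and 4, strict, start inferred | 31% | 72% |
| 2 and 4, random order | 11% | 72% |
| 4 and 6, random order | 6% | 69% |
| 4, 6 and 8, random order | 2% | 68% |

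At a small site of 10 infants, the three readings of the current scheme give about 33%, 21% and 10% certain, with best-guess rates of 70% to 71%.

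**Why a few infants could count.** Expected primary events: 550 × 0.01 = 5.5. As an illustration, assume 275 analysed per arm and a Wald 95% interval (the article names no interval method). Take 3 control events, close to the expected 275 × 0.01 = 2.75.

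- 5 oral events: difference 2/275 = 0.73%, standard error 1.02%, upper limit 2.73%, inside the 3% margin.
- 6 oral events: difference 3/275 = 1.09%, standard error 1.08%, upper limit 3.21%, outside it.

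In this example one event changes the conclusion.

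**The case against.** **The 39% is an upper figure.** It needs strict alternation, a known starting block, knowledge of the sizes, and staff who track every allocation. A reader might infer that 39% of allocations are simply knowable in advance. The documents do not support that as a fact, because the order is not spelled out beyond one word. The range is about 11% to 39%.

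**A journal article condenses.** Random ordering and non-disclosure of sizes may stand in the full protocol. This is right, and their absence here is not the point. The point is a choice the article does state: blocks as small as 2, within site, in open-label treatment.

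**The assurance about influence.** A reader might infer that predictability contradicts the statement that "Randomisation can under no circumstances be influenced by the study team". It does not. In context, next to the web-based programme, the sentence means that staff cannot alter the allocation, and prediction leaves the list untouched. The sentence is not wrong; it simply gives no protection against prediction.

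**The harm is not shown.** A reader might also infer that sicker infants would be kept from oral slots, so that the oral arm looks safer. The documents give no ground for that direction, since a clinician's preference could run either way, and nothing suggests that steering has occurred. Eligibility also narrows the room for it: infants must be clinically well with elevated markers, and proven bloodstream infection and severe disease are excluded. Discretion over whom to approach remains.

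**The remedy hardly changes the best-guess rate.** It falls only from 72% to 68% or 69%. This stands. Guessability is largely inherent in site-stratified blocks under open treatment. The gain lies in removing certainty.

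**Conclusion.** The point holds as a weakness in allocation concealment that follows from a stated design choice. Between about 11% (random order) and 39% (strict alternation, start known) of allocations are certain to an observer who knows the sizes and has seen all earlier allocations at the site, with about 31% in between if the start must be inferred. The 72% best-guess rate does not depend on which reading applies.

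The consequence is a risk of selective enrolment before randomisation, of unknown direction and size. It is neither a demonstrated bias nor an internal contradiction. It deserves attention because the result is expected to rest on 5 to 6 events and the correction is cheap. It is a cheap improvement, with medium confidence because the order and disclosure of the sizes cannot be settled from the article.

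**What to change.** For all remaining allocations:

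1. Drop blocks of 2.
2. Use larger blocks in random order within site, such as 4 and 6, or 4, 6 and 8.
3. Withhold the sizes from the sites. This step is essential, because identifying a slot as certain depends on knowing the sizes. It does not stop someone guessing the lagging arm from the running count, so some guessability remains.

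If random order and concealment were already in place, correct the word 'alternated' to say so, and still drop blocks of 2.

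The cost is a setting in the web randomisation programme and a sentence in the protocol. The downside is slightly looser balance: the largest possible imbalance at a site is half the largest block, so 3 infants (blocks up to 6) or 4 (blocks up to 8) in place of 2 now. That is minor with 550 infants in 17 hospitals.

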### Follow-up

Neonates will only be discharged from the hospital if they have shown to tolerate the oral antibiotic treatment for at least two doses and are clinically well. Parents will be interviewed by telephone on the first day after discharge and on day 14 after initiation of antibiotic therapy by the local study investigator or research nurse. The local investigator will assess antibiotic intake, signs of infection, side effects and events. In addition, parents will receive a survey on day 7 and day 21 with questions regarding possible signs of infection, side effects, QOL, loss of productivity, and cost-effectiveness and demographic data (maternal, paternal age, highest level of education, socioeconomic status and siblings). All surveys are available as online supplementary material. The primary outcome of the study is assessed 28 days after treatment completion, when the patient will be seen by the local investigator or research nurse for a final visit at the outpatient department. Parents of participants in the oral treatment group will be asked to return the bottle with remaining antibiotic suspension in order to evaluate medication adherence through measurement of the remaining amount of medication present in the bottle. Follow-up of neonates in the control group will be identical.

### Power calculation

Relapse of proven GBS infection is estimated to occur in 0%–8% of patients, but may be caused by a different strain.^17^ Two epidemiological studies estimated the recurrence rate to be 1% in proven bacterial neonatal infections.^18 19^ The current study focuses on probable infections (in which the recurrence rate is likely even lower, although evidence for this is lacking). The incidence of community-acquired late-onset sepsis in otherwise healthy neonates is low (~0.28 per 1000 live births).^20^ Therefore, we assume a 1% infection rate (including new non-related infections) in both groups. Based on a non-inferiority margin of 3% (minimum success rate 96%), 2×231 patients are needed for a power of 90% using a one-sided alpha of 0.025. Because of the first 30 patients undergoing PK measurements and uncertainty about the PK values, and potential drop-out or withdrawal (estimated approximately 5%–10%), we will include 2×275 neonates (total=550). A post hoc report on the design effect will be included.

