## Outcome measures and statistical analysis

### Primary outcome

The primary outcome is bacterial (re) infection within 28 days after finishing antimicrobial therapy, defined as clinical symptoms of infection and fever (>38.0°C) or hypothermia (<36.0°C) and elevated inflammatory parameters with a need for prolonged antimicrobial therapy for more than 48–72 hours. Proven or suspected viral infection, for which no antibiotics are initiated or antibiotics are stopped within 48–72 hours (after return of culture and/or viral results) are not considered as a bacterial (re) infection. A chart will aid in decision making with respect to differentiation between bacterial infection and other causes. Both per-protocol analysis and intention-to-treat analysis will be performed. A p<0.025 will be considered as significant. Regarding the primary outcome, 28-day cumulative bacterial infection rate; proportions will be defined and used to compare both treatment strategies. Subgroup analysis will be performed on late preterm neonates (gestational age 35–37 weeks). Further, mixed-effect models will be used to take into account the multiple centres.

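### The stated 90% power at one-sided 0.025 with 231 per arm rests on a normal approximation that fails at about 2.3 expected events per arm; score or Newcombe rules give about 73% at 231 and 80% at 275

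*Protocol article*

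**What the plan says.** All inputs are in the protocol article.

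- Power calculation: "we assume a 1% infection rate (including new non-related infections) in both groups". The margin is 3 percentage points, so the boundary is 96% versus 99% success, or 4% versus 1% infected.
- Power calculation: "2×231 patients are needed for a power of 90% using a one-sided alpha of 0.025". Recruitment is then raised to 275 per arm (550 in total), to allow for the pharmacokinetic patients and for 5%–10% drop-out or withdrawal.
- Randomisation and blinding: "Randomisation ratio will be 1:1".
- Primary outcome: "A p<0.025 will be considered as significant", and "proportions will be defined and used to compare both treatment strategies". Mixed-effect models for centre are mentioned in addition. No specific test or interval for the non-inferiority decision is named.

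**The concern.** At a 1% rate, 231 infants per arm yield about 2.3 expected events. With so few events the usual standard error of a difference in proportions is too small too often, and the difference is far from normally distributed. A sample size from the normal formula can then promise power and error control that no actual test delivers together.

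Two things are at stake. If the analysis uses a test that holds its level, a truly equivalent oral strategy fails to be shown non-inferior more often than the 10% the protocol accepts. If it uses the test that matches the sizing formula, an oral strategy truly 3 points worse is declared non-inferior more often than the stated 2.5%.

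**Working it through.** **1. Reproducing 231.** Unpooled normal formula, with p = 0.01 in both arms and margin 0.03:

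n = (1.96 + 1.2816)² × 2 × 0.01 × 0.99 / 0.03² = 231.16 per arm.

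This is the protocol's figure. Other variants tried do not give it: one-sided 0.05 gives 189, 80% power gives 173, and the Farrington–Manning null-variance formula gives 365.

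**2. Expected events.** 231 × 0.01 = 2.3 per arm; 275 × 0.01 = 2.75 per arm. The chance of no control events at 231 is 0.99²³¹ = 0.098.

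**3. Rules compared.** Non-inferiority is declared when the upper 95% limit for d (intervention minus control) is below 0.03.

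- Wald: d + 1.96 × √[p_I(1−p_I)/n + p_C(1−p_C)/n] < 0.03.
- Farrington–Manning score: (d − 0.03)/SE₀ < −1.96, with SE₀ from the estimates restricted to a difference of 0.03.
- Newcombe: d + √[(U_I − p_I)² + (p_C − L_C)²] < 0.03, with Wilson limits U and L.

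Largest number of intervention events accepted, for 0, 1, 2, 3, 4, 5 control events:

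| n per arm | Wald | Score and Newcombe |
|---|---|---|
| 231 | 3, 3, 4, 4, 5, 5 | 1, 2, 3, 3, 4, 4 |
| 275 | 4, 4, 5, 5, 6, 6 | 2, 3, 3, 4, 5, 5 |

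An example at 275 with 2 control events: for 5 intervention events the Wald limit is 0.0109 + 1.96 × 0.00955 = 0.0296, accepted. For only 4 the Newcombe limit is 0.0073 + √(0.02225² + 0.00528²) = 0.0301, not accepted.

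**4. Exact power and error.** Sum Bin(x_I; n, p_I) × Bin(x_C; n, p_C) over all accepted pairs. Power is at 1% versus 1%; one-sided error is at 4% versus 1%. The sizes 261 and 247 are 275 × 0.95 = 261.25 and 275 × 0.90 = 247.5, rounded down. Score and Newcombe agree at all four sizes.

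| n per arm | Score/Newcombe power | Score/Newcombe error | Wald power | Wald error |
|---|---|---|---|---|
| 231 | 73.1% | 2.0% | 88.9% | 4.9% |
| 247 | 74.0% | 1.8% | 90.2% | 4.1% |
| 261 | 79.8% | 1.9% | 90.7% | 4.1% |
| 275 | 79.6% | 1.9% | 93.2% | 4.6% |

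At 250 per arm the Wald error is 5.0% and the score error 2.1%. The results move unevenly with n because the counts are so small.

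**5. Could any test rescue the statement at 231?** Between (4%, 1%) and (1%, 1%) the likelihood ratio depends only on the intervention count, so the Neyman–Pearson test gives an upper bound on power. With n = 231, P(X ≤ 3) is 0.0163 at 4% and 0.7980 at 1%; P(X = 4) is 0.0280 at 4% and 0.1181 at 1%. The fraction of X = 4 that may be accepted is (0.025 − 0.0163)/0.0280 = 0.310. The bound is 0.7980 + 0.310 × 0.1181 = 0.835. No test holding 0.025 at 4% versus 1% can exceed 83.5%. At 275 the same bound is 90.1%, reached only by a randomised test that treats the control rate as known.

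**6. Sensitivity to the event rate** (score/Newcombe power, same rate in both arms).

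- 0.5%: 85% at 231, 90.5% at 247, 93% at 261 and 275.
- 2%: 52% at 231, 54% at 247, 58% at 261, 61% at 275.

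**7. Size that would give 90% at 1%.** About 340–350 evaluable per arm (at 350, 90.6%).

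**The case against.** **The arithmetic is right.** This stands. 231 is the correct output of a widely used formula. The fault is that the formula's two promised properties do not hold together at this event rate.

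**The analysis test is not stated, and an analysis plan may name a good one.** This stands as far as it goes. A reader might infer that the trial will use a Wald test and therefore has about double the stated error. The article does not say so; a planning formula does not fix the analysis, and leaving the interval to an analysis plan is normal. The error figures are conditional on Wald. Even then the inflation is about 1.6-fold at 247 and 261 per arm, the sizes left after the protocol's own loss, and nearer two-fold only at sizes such as 231, 250 and 275. The power statement gains nothing from this objection, because the 83.5% bound applies to every test that holds the level.

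**73% and 80% are not the power of every valid test.** Correct. They belong to score and Newcombe rules, whose error is below 2.5%. Cut-offs calibrated only at a 1% control rate give about 76%–82% at 231 and 83%–87% at 275, still short of 90%. Agresti–Caffo gives 83% and 90%, but its error is about 3.2%.

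**The true rate may be lower.** The Power calculation section thinks recurrence in probable infection is likely below 1%, while noting that evidence is lacking and that its 1% includes unrelated infections. At 0.5% a score test has 90% or more at 247 and above. This is a fair reason not to call the trial undersized, but it does not make the statement at 1% correct.

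**The reserve.** A reader might take the 30 pharmacokinetic infants and 10% loss off each arm, (275 − 30) × 0.9 = 220, and conclude that the trial falls below its own 231. The documents do not support this. The Pharmacokinetics section places those infants in the intervention arm only, and no section says that they are excluded from the primary analysis.

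**Conclusion.** The power statement is wrong as written. Under its own assumptions (1% in both arms, 3-point margin, one-sided 0.025), 231 per arm cannot give 90% power with any test that holds the level at 4% versus 1%; the ceiling is 83.5%. With score or Newcombe rules, power is about 73% at 231 and 74%–80% over 247–275 evaluable per arm, with error of 1.8%–2.1%. A truly equivalent strategy would then miss non-inferiority in about 20%–27% of trials, not 10%. If the Wald rule were used, error at 4% versus 1% would be 4.1%–5.0%.

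The figures assume independent infants, 1:1 allocation and an unadjusted comparison of proportions. They depend strongly on the event rate. A reader might conclude that the trial must grow to about 350 per arm; that does not follow, because the finding concerns the stated power and the choice of interval, and power at rates below 1% is considerably better.

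**What to change.** - Restate the power as about 73% at 231 per arm and 74%–80% at 247–275 evaluable per arm, under a 1% rate and a score or Newcombe rule.
- Add a short table over event rates from 0.5% to 2%. For the score rule the end points are 85% (231) and 93% (275) at 0.5%, and 52% and 61% at 2%.
- State that non-inferiority is decided by the upper limit of a two-sided 95% score (Farrington–Manning or Miettinen–Nurminen) or Newcombe interval for the risk difference against 3%, not by a Wald interval. Fix this before outcome data by arm are seen, because the rules differ at realistic counts.

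The cost is one rewritten paragraph, one added sentence and a less favourable stated power. The 550 need not change.
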